## Abstract

**Background:**

Females of reproductive age with concussion report a greater number of symptoms that can be more severe and continue for longer than age matched males. Underlying mechanisms for sex differences are not well understood. Short non-coding Ribonucleic Acids (sncRNAs) are candidate salivary biomarkers for concussion and have been studied primarily in male athletes. Female sex hormones influence expression of these biomarkers, and it remains unclear whether a similar pattern of sncRNA expression would be observed in females following concussion. This study aims to evaluate recovery time, the ratio of salivary sncRNAs and symptom severity across different hormone profiles in females presenting to emergency departments (ED) with concussion and, to investigate the presence of low energy availability (LEA) as a potential modifier of concussion symptoms.

**Methods:**

This prospective cohort study recruits participants from New Zealand EDs who are biologically female, of reproductive age (16–50 years) and with a confirmed diagnosis of concussion from an ED healthcare professional. Participants are excluded by ED healthcare professionals from study recruitment as part of initial routine assessment if they have a pre-diagnosed psychiatric condition, neurological condition (i.e., epilepsy, cerebral palsy) or more than three previously diagnosed concussions. Participants provide a saliva sample for measurement of sncRNA’s, and online survey responses relating to hormone profile and symptom recovery at 7-day intervals after injury until they report a full return to work/study. The study is being performed in accordance with ethical standards of the Declaration of Helsinki with ethics approval obtained from the Health and Disability Ethics Committee (HDEC #2021 EXP 11655), Auckland University of Technology Ethics Committee (AUTEC #22/110) and locality consent through Wellington hospital research office.

**Discussion:**

If saliva samples confirm presence of sncRNAs in females with concussion, it will provide evidence of the potential of saliva sampling as an objective tool to aid in diagnosis of, and confirmation of recovery from, concussion. Findings will determine whether expression of sncRNAs is influenced by steroid hormones in females and may outline the need for sex specific application and interpretation of sncRNAs as a clinical and/or research tool.

**Trial registration:**

Australian New Zealand Clinical Trials Registry (ANZCTR) registration number ACTRN12623001129673.

## Background

Concussion, as a subset of mild traumatic brain injury, is a brain injury induced by direct or indirect biomechanical force being transmitted to the head via a blow to the head or the body. Disturbance in cellular homeostasis in the brain initiates complex biochemical and neurometabolic changes [1] resulting in a transient ‘energy crisis’ in the brain. Concussion is typically considered a functional rather than structural injury and presents as a variable cluster of physical, cognitive, emotional, and sleep related symptoms. Sports Related Concussion (SRC) has become almost synonymous with male collision sport and has in recent years received increased profile and greater awareness generated through traditional and social media. However, concussion occurs in many activities and environments with data showing that sports collectively account for only 20–40% of all concussions. [2, 3] Motor vehicle accidents and military combat are other common mechanisms of injury in males, [4] whereas females have tended to sustain concussion from falls or incidents of intimate partner violence. [4] As greater numbers of females enter the armed forces and play collision sports, the incidence of concussion in these environments will likely increase. There is a need to ensure that both sport and non-sports related concussion are addressed in research and clinical settings, and in public awareness and media campaigns.

Sex differences are evident in concussion. [5–14] Females often have more severe symptoms that are longer in duration. [15–18] Studies in female athletes also show that symptom endorsement at baseline (i.e., when there is no injury) is more prevalent than that seen in males. [19] Underlying mechanisms for these observed sex differences are not yet well understood and sex as a biological variable in injury recovery remains understudied. [20] Limited data show that sex differences in concussion outcomes (i.e., severity and duration of symptoms) first appear during adolescence, are evident throughout the reproductive years, but that postmenopausal women have similar or better outcomes than men. [5] Women have a considerable physiologic change when transitioning between these life stages with altered levels of estrogen and progesterone. Bi-directional relationships between female sex hormones and concussion could influence symptoms and recovery outcomes. [4, 5, 21, 22] Primary female sex hormones, estrogen and progesterone are typically associated with reproduction, but these hormones are powerful biochemical messengers that influence every body system including, temperature regulation, macronutrient metabolism, hydration, central nervous system fatigue, and brain bioenergetics. [23–26] During reproductive years, estrogen and progesterone fluctuate across the menstrual cycle, which typically lasts 21–35 days. [27, 28] Hormone related symptoms have significant overlap with those symptoms associated with concussion and are similarly considered across physical, cognitive, emotional and sleep related domains. Low Energy Availability (LEA) occurs when dietary energy intake is insufficient to support energy expended in exercise and results in inadequate energy to support the functions required by the body to maintain optimal health; prolonged LEA is a clinical concern that disproportionately affects females, can disrupt endocrine function [29, 30] and presents with a similar set of symptoms to concussion. The prevalence of LEA ranges from 33.5% in recreationally active (tier 2 [31]) females [32] to 59% in sub-elite [33] (tier 3 [31]) and 88% in professional female football players [34] and could be a potential modifier in concussion. Female specific research is therefore needed to understand how sex hormones interact with concussion and to what extent concussion may impact hormone regulation and symptoms.

Diagnosis of concussion may not always be clear; assessment typically includes the use of neurocognitive and physical tests and subjective symptom report. It is also important to identify a plausible mechanism of injury, which can also be difficult to recognise in cases where there are multiple injuries. There are currently no validated tools or tests that can confirm a diagnosis of concussion, this relies on clinical judgement. Recent research in clinical settings and on sports field sidelines [35–45] indicated potential blood biomarkers that may be specific to concussion, including beta-amyloid protein, ubiquitin carboxy-terminal hydro-lase L1 (UCH-L1), glial fibrillar acidic protein (GFAP), S100β, Tau, neurofilament light protein (NFL) and brain derived neurotrophic factor (BDNF). [36–43]. However, due to relatively small heterogenous sample sizes and varying methodological approaches there have been inconsistent research findings and a lack of clarity on the time course or presence of these biomarkers in relation to injury. More recent advances in technologies have enabled investigation into ribonucleic acid (RNA) species as potential biomarkers of disease. [35, 37, 38, 41, 46] MicroRNAs (miRNAs, miRs) act at the post-transcriptional level to regulate protein synthesis and belong to the family of small non-coding RNAs (sncRNAs) (20 to 200 nucleotides in length). MiRNA signatures specific to traumatic brain injury (TBI) including concussion have been reported in blood, cerebrospinal fluid and saliva, and these signatures appear to vary according to TBI severity. Different ‘families’ of miRNA’s may be upregulated or downregulated in response to various conditions (e.g., post-exercise or injury) or disease states.

Non-invasive saliva sampling enables rapid collection of data immediately after injury and at specified time points thereafter, with the participant able to collect the sample independently. In a recent study [35] utilising a saliva collection protocol, a panel of 14 different sncRNAs present in saliva accurately discriminated between clinical diagnosis or absence of concussion in 156 professional male rugby union players. These sncRNAs have potential to provide objective insight into pathophysiological responses following a concussive injury and may be a useful adjunct as a sideline test and in the clinical environment to aid diagnosis. Findings of studies in male athletes cannot be extrapolated to female populations without further investigation, as expression of sncRNAs in other diseases of the central nervous system is sex dependent. [47–50]

## Methods/design

### Aim

The aims of this study are to: 1) determine if the time to recovery (in days) differs among groups categorised by their hormone profiles at the point of concussion injury, 2) examine whether the ratio of sncRNAs in saliva differ across groups categorised by their hormone profiles at the point of concussion injury, 3) assess whether self-reported symptoms differ among groups categorised by their hormone profiles at the point of concussion injury, and 4) investigate whether low energy availability changes across the recovery period, and if this is associated with symptoms experienced.

### Study design

The prospective cohort study design involves recruitment of participants from Emergency Departments (ED) in Wellington, New Zealand.

### Patient and public involvement

Patients and members of the public were involved in the choice of outcome measures and the recruitment strategy in development of this research protocol. During the study design women with and without experience of a brain injury provided input on the feasibility and participant burden associated with each outcome measure through early experimental work and through informal discussion. The recruitment strategy and dissemination plan were refined based on discussions with patients presenting to ED with suspected concussion.

#### Participants and recruitment

Females presenting to ED within three days of injury with suspected concussion are recruited by ED healthcare professionals. Participants are invited to participate if they are biologically female (self-report), of reproductive age (16–50 years) and have a confirmed diagnosis of concussion from the consulting healthcare professional. The diagnostic criteria for concussion are those outlined in the most recent international consensus statement from the concussion in sport group. [51] Participants will be excluded if they have Polycystic Ovarian Syndrome (PCOS), a pre-diagnosed psychiatric disorder or neurological condition (e.g. epilepsy, cerebral palsy) or if they have had more than three previously diagnosed concussions; these are known modifiers for prolonged recovery. [52, 53] These specific exclusion criteria will be ascertained by the consulting ED healthcare professional as part of the initial routine assessment for concussion. Full inclusion/exclusion criteria are shown in Table 1. The standard concussion assessment is detailed in Fig. 1. Study recruitment commenced February 2022, however there was interruption due to COVID related sickness and changes in the ED through November 2022. The study recommenced in January 2023 and is in progress.

**Table 1 Tab1:** Inclusion and exclusion criteria

Inclusion criteria	Exclusion criteria
Females of reproductive age: 16–50 years (with a menstrual cycle for a minimum of 2 years if naturally cycling)	Had three or more previously diagnosed concussions
Natural regular menstrual cycle 28–35 days long, or Currently taking Oral Contraceptive Pill (OCP), or Currently have Intra Uterine Device (IUD), or	Current concussion was more than 3 days ago
	Post-menopause
	Started taking medication that would alter reproductive hormone concentrations (Corticosteroids, e.g., Prednisone. Antidepressant or Antipsychotic medication) within the last 3 months
	Current clinical diagnosis of an eating disorder
	Pre-diagnosed psychiatric disorder
	Pre-diagnosed neurological condition
	Polycystic Ovarian Syndrome (PCOS)
	Oligomenorrheic (irregular periods), or
	Amenorrheic (loss of periods for 3 months or longer)
Confirmed diagnosis of concussion by a medical doctor (within 3 days of injury)	GCS^a^ score less than 15 at 4 h after initial assessment. These patients may be referred for a CT scan and will not be eligible for the study

In the context of acute brain injury scores of < 8 = Severe, 9–12 = moderate, 13–15 = mild

^a^*GCS* Glasgow coma scale is used to objectively describe the extent of impaired consciousness in all types of acute medical and trauma patients

**Fig. 1 Fig1:**
[figure not shown]
Routine clinical assessment and study flow

All participants will be over the age of 16 years and can therefore provide their own consent after reading a participant information sheet about the project. Participants will have the opportunity to ask questions of the research team prior to providing consent. Upon providing written consent, participants will be assigned a unique identifier number (e.g., CH001). If a healthcare professional advises that a patient may have temporary incapacity to provide consent due to the brain injury being treated at the ED, consent will be re-confirmed via follow up with the participant within three days using the contact information already provided on the consent form. Interpersonal violence (IPV) disproportionately affects females, to ensure safeguarding of any participants in this study that may be vulnerable the Te Whatu Ora (Health NZ) Family Violence Guidelines are implemented. [54] It is important that patients presenting to ED with injuries from IPV, assault or motor vehicle accidents are included as potential participants; concussion may often go unidentified due to polytrauma or an unrecognised mechanism of concussive injury. A specific concussion biomarker may be of most value in this cohort.

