#### Surveys and questions

Survey and question data are collected and managed using REDCap (Research Electronic Data Capture) which is a secure, web-based software platform designed to support data capture for research studies. [56, 57] Participants are provided with an online link to REDCap via email. A new link is sent every seven days after initial appointment until a full return to work/study is reported. It takes approximately 10 min to complete all questions each week.

Two concussion specific questions are asked only once, seven days after the initial appointment. The first question relates to concussion history and is utilised to capture the number of previous concussions the participant has had. This information is important as prior concussion can impact recovery from subsequent concussions. [52] The second question is used to capture whether the participant’s concussion is sport related or not.

Participants are also asked to complete the Low Energy Availability in Females Questionnaire (LEAF–Q) online seven days after initial assessment and then at seven-day time intervals throughout recovery. The LEAF-Q [58] is designed and validated to evaluate physiological symptoms of insufficient energy intake or low energy availability (LEA). The LEAF-Q contains questions regarding injuries, gastrointestinal and reproductive function. In Sect. 3.2 three questions (19 items) relate to menstrual function including recent menstrual history. This questionnaire section is used to determine hormonal profile of participants and has been modified as outlined below.

Part C of Sect. 3.2 includes the following question:C: Do you have normal menstruation? Yes ☐ No (go to question C6) I don’t know (go to question C6)C1: If yes, when was your last period? 0–4 weeks ago ☐ 1–2 months ago ☐ 3–4 months ago ☐ 5 months ago or more ☐

This question has been modified to capture more accurate detail about the last menstrual cycle as follows:C: Do you have normal menstruation? Yes ☐ No (go to question C6) I don’t know (go to question C6)C1: If yes, when was your last period? 1 week ago ☐ 2 weeks ago ☐ 3 weeks ago ☐ 4 weeks ago ☐ 1–2 months ago ☐ 3–4 months ago ☐ 5 months ago or more

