Participants are categorised into one of five hormone profiles as follows; 1) Follicular phase if question C1 is answered as “1 week ago”, 2) Mid-cycle if question C1 is answered “2 weeks ago”, 3) Luteal phase if question C1 is answered “3 weeks ago” or “4 weeks ago”, 4) Oligomenorrheic if C1 was answered “1–2 months ago”, “3–4 months ago” or “5 months ago or more”, 5) Using contraceptive if question 3.1a is answered “yes”.

Scoring of question 3.2 remains the same, i.e., if a participant ticks any of the boxes within the 0–4 weeks’ timeframe the same score is applied as the original question. In eumenorrheic participants this will help estimate menstrual cycle phase at point of injury. This information is used to understand any association between hormonal profile and or LEAF_Q score with symptom severity and duration of concussion.

The Brain Injury Screening Tool (BIST) is a brief screening tool for use on initial presentation after injury to guide health care pathway decision making and to monitor symptoms and recovery over time. [59] The BIST was developed in the NZ context to fit the clinical environment and to provide consistency across multiple environments and referral pathways (e.g. GP clinic, ED, Urgent Care Centres), the tool has also been psychometrically tested. There are two sections in the BIST; the first section is used to determine if there are any clinical ‘red flags’ which require referral to hospital, therefore this component is not included in this study. The second section of the BIST includes a 16-item symptom report scale for patients to rate how much they now experience the symptoms listed on a scale of 0 (not at all) to 10 (severe). Higher symptom scores are indicative of higher symptom burden. Participants are asked to complete this part of the BIST at point of presentation with injury and at seven-day time intervals throughout the study to monitor symptoms and recovery over time.

The final question asks if the participant has made a full return to work/study and how many follow-up appointments they had. The number of days between injury and full return to work/study will be used as a proxy for recovery. This question is included in the weblink sent at all timepoints (i.e., 7, 14, 21, 28 days etc.) until the participant reports they have achieved a full return to work/study, at which point participation in the study will be complete. Detail of information collected each week is included in Table 2.

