**Table 2 Tab2:** Research measures and collection points

Measure	How	Who	When		
			Initial assessment	During recovery (7-day time intervals)	Full return to work/study
Saliva Samples	Passive drool into cryovial	Consulting clinician, research assistant or Lead Researcher	X		
Number of prior concussions^b^	Online^a^	Participant to complete		X	
Sport or non-sport related concussion^b^	Online^a^	Participant to complete		X	
LEAF-Q	Online^a^	Participant to complete		X	
BIST	Online^a^	Participant to complete	X	X	
Number of days from injury to recovery (full return to work/study)	Online^a^	Participant to complete			X

^a^Weblink emailed to participant

^b^Question only asked once, at first (7-day) timepoint

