### Strengths and limitations of the study

This is the first study to consider the impact of fluctuating female sex hormones on salivary sncRNA expression following concussion. Limitations of this study are that it relies on self-report hormone profiles and does not include verification using the ‘gold standard’ approach [66]. Menstrual cycle information is based on recall which can be subject to bias and inaccuracy. Return to work is being used as a proxy for recovery from concussion which does not necessarily reflect full physiological recovery. Information regarding treatment interventions and follow up appointments for each participant will not be collected, it will therefore not be known how the ongoing management may influence the recovery time. One further limitation could the relatively small sample size compared the number of variables under investigation. The power calculation is based on the primary aim of the study.

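### Women with other injuries are deliberately kept eligible, but the Aim 1 event is unqualified return to work or study and no item separates concussion from another injury as the cause of delay

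*Protocol article*

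**What the plan says.** **Who is enrolled.** The consent and safeguarding paragraph under Participants and recruitment says: "It is important that patients presenting to ED with injuries from IPV, assault or motor vehicle accidents are included as potential participants". Its reason is that "concussion may often go unidentified due to polytrauma or an unrecognised mechanism of concussive injury". Table 1 excludes several medical and hormonal conditions and patients below a consciousness-score threshold. It contains no limit on injuries elsewhere in the body.

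**What is counted as recovery.** Under Surveys and questions: "The number of days between injury and full return to work/study will be used as a proxy for recovery". It comes from a self-report item sent weekly: "The final question asks if the participant has made a full return to work/study and how many follow-up appointments they had". Table 2 lists the same measure, and Data analysis treats it as time to recovery from concussion in a Cox model by hormone profile.

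**What else is recorded.** The injury-context items are the number of previous concussions and one on sport: "The second question is used to capture whether the participant’s concussion is sport related or not". The LEAF-Q, sent weekly, includes questions on injuries. The BIST gives a 16-item symptom score at presentation and weekly. Neither is given a role in explaining why a woman has not returned.

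**What is conceded.** Strengths and limitations says: "Return to work is being used as a proxy for recovery from concussion which does not necessarily reflect full physiological recovery". It adds: "Information regarding treatment interventions and follow up appointments for each participant will not be collected".

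**The concern.** Aim 1 concerns recovery from concussion. In a woman who also has, say, a fracture that keeps her from work, the recorded day is the later of two recoveries, and the second has no stated link to hormone profile. She counts as not recovered from concussion for as long as the other injury lasts. The protocol wants to include the patients in whom this is most likely.

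At stake is the primary comparison. Mixing in an unrelated delay pulls the hazard ratio towards 1 in a study sized at 30 analysed women for a hazard ratio of 1.5. A statistical analysis plan could specify an adjustment, but it cannot adjust for information that was not collected.

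**Working it through.** **1. The plan's own figure.** Inputs from Sample size calculation: log hazard ratio B = 0.4055, covariate SD 1.5, R² 0.2, event rate 0.9, 80% power, type I error 0.05 (two-sided reproduces the result).

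N = (1.960 + 0.842)² / [0.9 × (1 − 0.2) × 1.5² × 0.4055²] = 29.47, so 30. With 20% dropout, 30 / 0.8 = 37.5, so 38. Both stated figures reproduce, and power at 30 is 80.7%. The sample size arithmetic is not in question. It assumes that the hazard ratio of 1.5 acts on the event as measured.

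**2. How dilution arises.** *Assumed, not in the documents:* concussion time is exponential with mean 14 days in the reference profile and a hazard 1.5 times higher in the comparison profile. A share q of women have another injury with an exponential time off work of mean m × 14 days, unrelated to profile. They return at the later of the two times. Only the ratio m matters, not the 14 days.

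Hand check at day 14 with m = 2:
- No other injury: returned = 1 − e^(−1) = 63.2% versus 1 − e^(−1.5) = 77.7%, a gap of 14.5 percentage points.
- Other injury: multiply each by the chance that the other injury has also cleared, 1 − e^(−0.5) = 39.3%. This gives 24.9% versus 30.6%, a gap of 5.7 points.

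**3. Observed hazard ratio for a true 1.5.** Simulated large samples, two groups, follow-up cut where 90% have returned (the plan's event rate):

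| Share with other injury | Women out of 30 | Observed HR, m = 2 to 4 |
|---|---|---|
| 10% | 3 | about 1.42 to 1.38 |
| 20% | 6 | about 1.36 to 1.26 |

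Simulation error is about 0.01. With m = 1, the observed value stays near 1.41 to 1.46 over the same shares.

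**4. Effect on power.** This uses the plan's own setting, a continuous covariate with SD 1.5, under the same mixing and 90% events. Power at N = 30 is Φ(√(30 × 0.9 × 0.8) × 1.5 × B_observed − 1.96).

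| Share | m = 1 | m = 2 | m = 4 |
|---|---|---|---|
| 10% | HR 1.45, power 74% | HR 1.40, power 65% | HR 1.35, power 54% |
| 20% | HR 1.41, power 67% | HR 1.34, power 53% | HR 1.26, power 37% |

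Example, 20% and m = 2: B_observed = ln 1.337 = 0.290, so 4.648 × 1.5 × 0.290 − 1.96 = 0.06, and Φ(0.06) is about 0.53.

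**5. What an other-injury flag recovers.** Adding the flag as a covariate to the Cox model in the step 3 scenarios brings the estimated hazard ratio back to about 1.45 to 1.49 at 10 to 20%.

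**The case against.** **It is a declared proxy with a stated limitation.** True, and the document does not contradict itself on the choice of proxy. But the stated limitation is of a different kind: a woman may be back at work before her brain has fully recovered. It does not say that she may be kept away after the concussion has cleared. The limitation on treatment data does not cover this either. Surveys and questions says that the number of follow-up appointments is asked, while the limitations say that such information is not collected. Either way, a count of appointments would not identify the cause of delay.

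**Some relevant information may already exist.** This stands in part. A reader might infer that nothing about other injuries is recorded, and the document does not support that. The LEAF-Q has injury questions, and weekly BIST scores could reveal a woman whose symptoms have cleared but who has not returned. The full survey form and Fig. 1 are not shown. What holds is narrower: no described item is assigned to attribute non-return.

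**Other injuries could create a false profile effect.** A reader might infer this from small groups. If 3 of 8 women in one profile and 1 of 8 in another were injured, the apparent hazard ratio with no true effect would be about 0.69 to 0.78. But with 8 versus 8 women and no injuries at all, the middle half of estimates already runs from roughly 0.7 to 1.4. Injury unrelated to profile adds noise and does not inflate the type I error, and the document does not give group sizes. The supportable concern is dilution.

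**The dilution could be worse.** Without censoring, the simulated hazard ratios are lower, about 1.22 to 1.30 at 20%. The plan assumes a 90% event rate, so the milder figures in the working are the relevant ones.

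**Conclusion.** The gap is real. Eligibility deliberately includes women likely to have other injuries, the Aim 1 event is return for whatever reason, and no described measure is used to separate the causes.

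Its size cannot be fixed from the document. The share of affected women, the length of their other absence and the exponential shapes are all assumptions. On those assumptions, and at the plan's event rate, a hazard ratio of 1.5 shrinks to about 1.38 to 1.42 at 10% affected and 1.26 to 1.36 at 20%. If other injuries clear as fast as the concussion, the loss is modest.

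This does not invalidate the study, and the inclusion should not be reversed. A reader might also infer that the primary event must be replaced by a concussion-attributed date. The document does not support going that far: 14 of 38 women had started by the last stated count, so a change of event could leave one cohort with two definitions of its primary outcome. The point is a cheap improvement that should be made while recruitment continues.

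**What to change.** Keep the inclusion and the existing primary event, and add the following:

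1. At the ED visit, record yes or no: is another injury present that could by itself delay return to work or study? For women already enrolled, take this from ED notes.
2. In the weekly form, for women not yet fully returned, add one item: is this because of concussion symptoms, another injury, or another reason?
3. Include the other-injury flag as a covariate in the Aim 1 Cox model.
4. Add a sensitivity analysis that uses concussion-attributable return or excludes women with such an injury.
5. Extend the stated limitation to say that other injuries can delay return.

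**Cost.** Two items in existing forms and a minor amendment, with no extra visit. Attribution is self-reported. Reason data will be incomplete for the women already enrolled; at the last stated count, 38 − 14 = 24 were still to start. One more covariate enters a model fitted to a small sample.
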